## Methods: Data collection, management, and analysis

### Data collection

Table 6 summarizes the schedule of enrolment, intervention, and assessments.

**Table 6 Tab6:**
[figure not shown]
Schedule of enrolment, intervention, and assessments (as per SPIRIT [22])

^1^PCT will be repeated after 6 to 24 hours in all admitted patients who did not receive antibiotics because of a low PCT value and in those in whom the algorithm was overruled

^2^In the subgroup of patients discharged home without antibiotics: phone evaluation after 48 hours

^3^Study D7, D28 and D90 are done by phone by the study team

^4^Biobanking of plasma, whole blood, paxgene tubes, urine, nasopharyngeal and oral swabs and sputa

^5^Urine biobanking (urine metabolites) in a subgroup of patients

^6^Optional interview for qualitative assessment of acceptability of the algorithm in a subgroup of patients

### At enrolment

Study data will be collected (from the patient and/or the medical file) by the study team in an eCRF developed on the electronic data collection (EDC) system REDCap®, hosted at Lausanne University Hospital [35, 36]. Data collected at inclusion includes demographic characteristics, comorbidities, symptoms and their duration, vitals and clinical signs, diagnostic tests required by the ED physician for LRTI management of the included patients (chest X-ray, CT-scan, LUS, CRP, PCT, white blood cell count, blood chemistry, blood gas, microbiology tests), destination on ED discharge, and antibiotic prescription. During the intervention period, the data collection will also include PCT results and LUS interpretation. Furthermore, physicians will record all their LUS images and videos following the aforementioned procedure in a secured drive.

A collection of biological samples (blood, respiratory, and urine) is performed parallel to the intervention trial as a study data-linked biobank. This includes a collection of nasopharyngeal and oral swabs, sputa if available, whole blood, plasma, PAXgene™ blood RNA system tubes, and urine samples at inclusion in all study centers. Furthermore, urine samples are collected on day 7 in the University Hospital of Lausanne and the Cantonal Hospital of St Gallen.

### During follow-up

Study data will be collected by phone on days 7, 28, and 90. The study team will perform the follow-up phone calls. If the patient is admitted on the day of follow-up, the study team will interview the patient. They will also use the patient’s medical file if relevant. Data collected at follow-up includes mortality, hospitalization, use of oxygen therapy or non-invasive ventilation, presence of local complication of pneumonia, use of antibiotics, health care resources, LRTI-related symptoms, and evaluation of quality of life.

### Data management

Study data will be collected via an electronic case report form (eCRF) and managed using REDCap®. Trial and participants’ data will be handled with uttermost discretion and is only accessible to authorized personnel who require the data to fulfil their duties within the scope of the study. On the CRFs and other study-specific documents, participants are only identified by a unique participant number (3 to 4 letters for the site followed by 3 digits for the patient). Coding is generated by using the eCRF software. Biological material in this study is not identified by participant name but by a unique participant number. Biological material is appropriately stored in a restricted area only accessible to the authorized personnel.

Each recording and transcript collected during the qualitative interviews will be identified by the patient’s or physician’s unique participant number. To further ensure confidentiality, transcripts will be coded for any name or place that could allow to identify a participant.

### Quality management and monitoring

#### Monitoring

The monitoring activities are coordinated by the Clinical Research Center (CRC) Lausanne. The Clinical Trial Center Zurich (members of the Swiss Clinical Trial Organization (SCTO) and CTUs Network) is contracted by Lausanne to perform monitoring activities at some local sites.

A risk-adapted monitoring strategy were developed according to the SCTO guidelines (Guidelines for Risk-Based Monitoring, version 3.0). The monitoring strategy (nature and extent of the monitoring activities) were described in a monitoring plan. Site initiation visits were conducted on each site before the start of the trial. Then interim monitoring visits (6 per site) will be performed on site and focusing mainly on safety and patient eligibility. A closeout monitoring visit per study site will be performed at the end of the trial to ensure all pending actions are resolved and study documentation is ready for archival.

#### Quality controls

The quality controls include the evaluation of study center compliance to the protocol. Non-adhesion to the algorithm will be escalated to the sponsor as a study deviation triggering corrective action from the investigators. Furthermore, non-adherence to the algorithm recommendation will trigger automatic alerts sent to the sponsor for direct feedback to the clinician in charge. There will be a monthly follow-up of deviation from the research proposal. This includes an implementation evaluation of the intervention to detect problems, which may be corrected.

#### Safety monitoring

In our study, an adverse event (AE) is defined as any untoward medical occurrence in a participant which does not necessarily have a causal relationship with the trial procedure. A serious adverse event (SAE) is defined as any untoward medical occurrence that results in death or is life-threatening, requires in-patient hospitalization or prolongation of existing hospitalization, results in persistent or significant disability or incapacity, or causes a congenital anomaly or birth defect. Occurrence of SAEs from the first participant visit until the last follow-up phone will be actively sought. All SAEs occurring during the study will be documented in the eCRF and followed until resolution. SAEs identified as related to the intervention will be notified to the Ethics Committee according to regulatory requirements, as well as immediate safety and protective measures that should be taken during the conduct of the study.

#### Protocol amendments

The Sponsor is authorized to amend the protocol. All important protocol modifications will be first discussed within the Steering committee and then communicated to the relevant parties (local investigators, EC, trial registry) by the Sponsor. Substantial amendments will only be implemented after approval by the EC, whereas non-substantial amendments are communicated by the Sponsor to the EC within the annual safety report. Under emergency circumstances, deviations from the protocol to protect the rights, safety, and well-being of patients may proceed without prior approval of the EC. Such deviations shall be documented and reported by the Sponsor to the EC as soon as possible. Amended protocols will be sent to the study sites for filling in the Investigator Site File, and training on new documents will be documented on site.

### Analyses

#### Sample size

The study is designed to demonstrate non-inferiority of the intervention in term of clinical failure occurrence and superiority in term of reducing antibiotic prescription. We plan to include 1530 patients in 9 study centers. Every study center will recruit 170 patients over about 2 years.

According to a stepped-wedge cluster-randomized design with a control period plus nine switch periods (steps) and the same number of clusters (one switch to intervention at each step), a mean number of 15 patients per unit and per time period will guarantee a 80% power (one-sided type I error *α* = 0.05) to prove non-inferiority regarding clinical failure (safety), if the proportion of clinical failure is 20% in both groups, with a non-inferiority margin of 10%, and assuming an intra-cluster correlation (ICC) of 0.2 and a coefficient of variation (cv) of the number of patients across units of 0.3. With 15 patients per unit and per time period, we would obtain a total sample size of 1350 (15 × 9 × (9+1)) patients. Further considering a 10% of lost to follow-up, we anticipate 15/0.9 = 17 patients per unit and per time period, leading to our final sample size of 1530 (17 × 9 × (9+1)) patients.

In our calculation, the ICC of 0.2 is based on results of a previous trial, the UltraPro trial [37]. The coefficient of variation of 0.3 in the number of patients between units is intended to allow for some variability between centers in the number of patients recruited. With an average number of 15 patients per cluster and per step, this corresponds to admitting that 95% of the clusters will recruit between 6 and 24 patients per step (between 60 and 240 in total). Correcting for 10% loss to follow-up, the same range will be between 67 and 267.

Of note, the 10% non-inferiority margin is supported by US FDA recommendations for anti-infectious trials assessing clinical success of a new treatment [38]. Sample size calculation with a 5% margin would lead to 5100 patients jeopardizing the feasibility of the trial.

This sample size in the framework of a stepped-wedge design guarantees a power of more than 90% to prove superiority regarding antibiotics prescription (efficacy), if the proportion of antibiotics prescribed is 0.65 in the control group and 0.5 in the intervention group (*α* = 0.05).

The sample size was calculated with R software, based on the manuscripts by Hemming et al. [39] and Harrison et al. [40].

### Statistical analyses

#### Datasets to be analysed, analysis populations

All analyses will be carried out in the primary analysis population, which includes all enrolled patients following an intention-to-treat principle. Any missing data at the enrolment visit due to incomplete documentation of the pre-assigned components of the algorithm will lead to the patient being assigned to the intention-to-treat analysis. Patients who are lost to follow-up will be replaced by additional patients’ inclusion as mentioned in the sample size (10% additional patients to compensate for loss to follow-up). Patients lost to follow-up will not be included in the analysis (complete case analysis). The primary efficacy and safety analyses will be repeated on the per-protocol population. The per-protocol population includes all patients who received all components of the PLUS algorithm without overruling on admission and 6–24 h later.

Stratified analyses will be done for severe LRTIs and non-severe LRTIs based on CRB-65 and PSI scores.

A sensitivity analysis will include patients who received a component of the intervention (PCT or LUS) while in the “usual care group” to evaluate if there is still an impact of the intervention when these tests are part of the usual care.

Additional analysis adjusting for patient level confounding factors (age, asthma, chronic obstructive pulmonary disease, CRB-65, and PSI score) in the intention-to-treat analysis will be done for both co-primary endpoints.

We will develop a detailed data analysis plan for secondary, subgroup, stratified, and sensitivity analyses. All analyses will be done with R Statistical Software.

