Item 4. What (procedures): Describe each of the procedures, activities or processes used in the intervention, including any enabling or support activities	Participants are managed by the physician in charge with the PLUS-algorithm. A pneumonia clinical prediction score (Van Vugt) is calculated automatically by the algorithm in the eCRF, physicians perform a LUS. In case of pneumonia on LUS and/or elevated clinical prediction score, PCT is measured. The algorithm recommends antibiotics in case of elevated PCT (≥ 0.25 μg/L). In patients with features of pneumonia on LUS and a low PCT, severity score (DS-CRB-65) is calculated. The algorithm recommends antibiotics in patients with a high severity score.	Participants are managed as usual. The physicians decide on antibiotic prescription as they usually do (usually based on a chest X-ray and blood tests)
Item 5. Who provided: For each category of intervention provider (for example, psychologist, nursing assistant), describe their expertise, background and any specific training given	Physicians in charge in the ED, have received a one-hour presentation on the scientific rationale behind the algorithm, a two-hour e-learning training on LUS, and a one-hour theoretical and two-hour practical training by an experienced instructor in LUS	Physician in charge in the ED have received a one-hour training on epidemiology and management of CAP in Switzerland based on Swiss guidelines [26] as well as explanations on the background of the study
Item 6. How: Describe the modes of delivery (such as face-to-face or by some other mechanism, such as internet or telephone) of the intervention and whether it was provided individually or in a group	Face-to-face individual meeting	Face-to-face individual meeting
Item 7. Where: Describe the types of location where the intervention occurred, including any necessary infrastructure or relevant features	ED	ED

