Item 8. When and how much: Describe the number of times the intervention was delivered and over what period of time, including the number of sessions, their schedule, and their duration, intensity or dose	The intervention is delivered once during ED management. PCT will be repeated after 6 to 24 hours in a subgroup of patient (all admitted patients who did not receive antibiotics because of a low PCT value and in those in whom the algorithm was overruled). In case of worsening disease within 28 days of enrolment in patients who did not receive antibiotics, reassessment will be done, and PCT will also be repeated.	Once during ED management
Item 9. Tailoring: If the intervention was planned to be personalized, titrated or adapted, then describe what, why, when and how	Not applicable	Not applicable
Item 10. Modifications: If the intervention was modified during the course of the study, describe the changes (what, why, when, how)	Not applicable	Not applicable
Item 11. How well (planned): If intervention adherence or fidelity was assessed, describe how and by whom; if any strategies were used to maintain or improve fidelity, describe them	The study monitoring plan includes the evaluation of study center compliance to the protocol and, non-adhesion to the algorithm will be escalated to the sponsor as a study deviation. Non-adhesion to the algorithm AB recommendation also triggers automatic alerts to the sponsor for direct feedback to the physician in charge.	Not applicable
Item 12: How well (actual): If intervention adherence or fidelity was assessed, describe the extent to which the intervention was delivered as planned	We will describe if the intervention was delivered as planned. Patients with incomplete intervention on day 0 will only be analyzed in the intention-to-treat analysis.	Not applicable

*AB* antibiotic, *CAP* community-acquired pneumonia, *eCRF* electronic case report form, *ED* emergency department, *LRTI* lower respiratory tract infection, *LUS* lung ultrasound, *PCT* procalcitonin, *TIDieR* Template for Intervention Description and replication

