### Control group

The comparator will be routine care. Physicians working in an ED during the control period will manage the patients as they usually do. Physicians are provided with the guidance for CAP from the Swiss Society of Infectious Diseases (SSI) to standardized practices [26]. However, decisions on antibiotics and on the use of diagnostic tests are left to the physicians.

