We expect that there will be some overruling, when antibiotic prescription is not recommended. To decrease the risk of overruling, we presented the rationale behind the algorithm during the site initiation visits. In patients in whom the algorithm is overruled and antibiotics are prescribed in spite of the recommendation of the algorithm, PCT will be repeated after 6–24 h. In case of low PCT levels, it will be recommended to stop antibiotics. A close monitoring will be performed to rapidly detect and correct non-compliance problems.

The PLUS algorithm based on clinical scores and easy-to-use diagnostic tests has the potential to improve the identification of patients with a LRTI who will benefit from antibiotics and reduce unnecessary antibiotic treatments. This diminished prescription of antibiotics will decrease side effects, cost, and resistance which are global health problems. The World Health Organization Trial Registration Data Set for PLUS-IS-LESS study is displayed in Table 7.

**Table 7 Tab7:** World Health Organization Trial Registration Data Set for PLUS-IS-LESS study

Data category	Information
Primary Registry and Trial Identifying Number	www.ClinicalTrials.gov, NCT05463406
Date of Registration in Primary Registry	19 June 2022
Secondary Identifying Numbers	BASEC number 2022-00738
Trial Protocol version	Study protocol V3.0 dated 28.02.2023
Source(s) of Monetary or Material Support	Grant: SNSF 33IC30_201300
Primary Sponsor	CHUV
Secondary Sponsor(s)	Not applicable
Contact for Public Queries	[name], [contact]
Contact for Scientific Queries	[name], [contact]
Public Title	Procalcitonin and Lung Ultrasonography Guided Antibiotherapy in Emergency Departments, The PLUS-IS-LESS study
Scientific Title	Procalcitonin and Lung UltraSonography based antibiotherapy in patients with Lower rESpiratory tract infection in Swiss Emergency Departments: a pragmatic stepped-wedge cluster-randomized trial
Countries of Recruitment	Switzerland
Health Condition(s) or Problem(s) Studied	Lower respiratory tract infections

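### The per-protocol set has no rule for usual-care patients and excludes overruled patients, so its antibiotic repeat selects on its own endpoint and its safety repeat carries selection bias of unknown direction

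*Protocol article*

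**What the plan says.** The section on datasets and analysis populations makes intention-to-treat primary: "All analyses will be carried out in the primary analysis population, which includes all enrolled patients following an intention-to-treat principle". It then adds: "The primary efficacy and safety analyses will be repeated on the per-protocol population". Membership of that second set is defined in one sentence: "The per-protocol population includes all patients who received all components of the PLUS algorithm without overruling on admission", and again 6–24 h later.

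Table 3, item 12, adds a related rule in the intervention column: "Patients with incomplete intervention on day 0 will only be analyzed in the intention-to-treat analysis". The usual-care column of that item is marked not applicable. Under Control group, usual-care physicians work without the algorithm: "decisions on antibiotics and on the use of diagnostic tests are left to the physicians".

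The Reassessment section describes overruled patients as those given antibiotics despite the algorithm's advice. The Discussion anticipates them: "We expect that there will be some overruling, when antibiotic prescription is not recommended". No rate is given. The efficacy endpoint (Endpoints, Table 4) counts any antibiotic prescription up to day 28.

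**The concern.** A per-protocol repeat of a between-arm comparison needs a membership rule for both arms. This one is written wholly in terms of receiving and following the algorithm, which usual-care patients never do.

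The exclusion criterion is also a treatment decision taken after enrolment. For the antibiotic endpoint that decision is the outcome itself. For clinical failure it may be related to how ill the patient looked, and it is applied in one arm only.

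What is at stake is the supportive analysis. In a non-inferiority trial, overruling brings the intervention arm closer to usual care and can dilute a real difference, so readers look to the per-protocol result for reassurance. If that result is itself shaped by selection, it cannot give it. Analysts are not blinded (Blinding), so a gap in the definition that is settled only once data are in hand would be hard to defend.

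**Working it through.** **The plan's own figures.** 15 × 9 × 10 = 1350; 15/0.9 = 16.7, rounded up to 17; 17 × 9 × 10 = 1530. Both reproduce. They concern the full set and do not depend on the per-protocol definition.

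**Step 1: who qualifies.** The rule requires the algorithm's components and no overruling. Usual-care patients have no algorithm to receive or overrule. The set therefore contains either no controls (literal reading) or all controls unfiltered beside a filtered intervention arm. The separate sensitivity analysis of usual-care patients who had PCT or LUS does not supply a per-protocol rule for controls.

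**Step 2: antibiotic endpoint.** Inputs: 65% control prescribing (Sample size); share *o* of all intervention patients removed as overruled by prescribing (assumed). Every removed patient is an event, so the kept rate is (p − o)/(1 − o). With no true effect, p = 0.65:

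- o = 0.10: 0.55/0.90 = 61.1%, difference −3.9 points
- o = 0.20: 0.45/0.80 = 56.3%, difference −8.8 points
- o = 0.30: 0.35/0.70 = 50.0%, difference −15.0 points

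The last row equals the whole planned effect (65% to 50%). I used a stepped-wedge generalised least squares standard error (9 clusters, 10 periods, 15 per cell, ICC 0.2, intervention cells shrunk by 1 − o, p(1 − p) taken as total variance). The chance of a significant result in favour of the algorithm, nominally 2.5%, becomes about 15%, 52% and just over 90%.

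**Step 3: is the kept rate the full-adherence rate?** Assume the algorithm recommends antibiotics in r = 40% and that 25% of the no-antibiotic recommendations are overruled. For initial prescribing:

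- intention-to-treat: 0.40 + 0.60 × 0.25 = 55%
- per-protocol: 0.40/(0.40 + 0.60 × 0.75) = 0.40/0.85 = 47%
- full adherence: 40%

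The per-protocol figure lies between the other two and estimates neither.

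**Step 4: clinical failure.** Inputs: 20% control failure and a 10-point margin (Sample size); share o and the risk ratio RR of failure, overruled versus kept (both assumed). Kept failure is p/(1 − o + o × RR). Put the truth at the margin, 30% versus 20%, where the one-sided error should be 5%. For example, o = 0.20 and RR = 2 gives 0.30/1.20 = 25.0%, an apparent difference of 5.0 points. The standard error is 0.0346 at o = 0.10 and 0.0356 at o = 0.20. The chance of declaring non-inferiority is Φ[(0.10 − difference)/SE − 1.645].

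| RR | Difference, o = 10% | Chance | Difference, o = 20% | Chance |
|---|---|---|---|---|
| 0.5 | 11.6 | 2% | 13.3 | 0.5% |
| 1 | 10.0 | 5% | 10.0 | 5% |
| 1.5 | 8.6 | 11% | 7.3 | 19% |
| 2 | 7.3 | 20% | 5.0 | 40% |
| 3 | 5.0 | 42% | 1.4 | 78% |

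Differences are in percentage points. The direction depends entirely on RR.

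**The case against.** **Intention-to-treat is primary.** The decision rules under Primary safety and efficacy endpoints do not mention the per-protocol set, and nothing requires the two to agree. This stands, and it limits the severity.

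**A separate analysis plan may complete the definition.** The article promises one for sensitivity analyses, and keeping all controls is the natural completion. That would settle the comparator. It would not undo the exclusion of overruled patients, which the article fixes.

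**A reader might infer that the safety repeat is biased toward non-inferiority.** That holds if physicians overrule in sicker patients, which is plausible but stated nowhere. Overruled patients also received antibiotics and may fail less. They were managed more like usual care, so removing them can expose harm that intention-to-treat dilutes. Overruling by withholding a recommended antibiotic, if counted, would remove a different kind of patient. The documents do not settle the direction.

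**A reader might treat the gap between intention-to-treat and per-protocol prescribing as pure artefact.** That takes intention-to-treat as the truth for an analysis meant to describe adherent use. Step 3 shows why this goes too far. What survives is that the repeat cannot serve as confirmation.

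**A reader might take the requirement for all components literally,** so that patients with a low score and negative ultrasound, who get no PCT by design, drop out. The algorithm is branched: "In case of pneumonia on LUS and/or elevated clinical prediction score, PCT is measured". The populations section also refers to pre-assigned components, so a branch-specific meaning is the likely one. Only a clarification of wording is needed.

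**Conclusion.** The point holds for the supportive per-protocol analysis. As written, the set either lacks a comparator or selects in one arm.

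For antibiotics the selection is on the endpoint and favours the algorithm mechanically: 3.9, 8.8 and 15.0 points with no true effect when 10%, 20% and 30% of intervention patients are removed. These sizes rest on assumed overrule shares and on overruling meaning prescribing, as the article describes it.

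For safety the bias has no known direction. With 20% overruled and the truth at the margin, the false non-inferiority rate runs from about 0.5% (RR 0.5) through 5% (RR 1) to 78% (RR 3).

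The primary intention-to-treat tests, the 1530 patients and the stated power are untouched. This should be fixed before analysis, but it does not threaten the primary conclusions.

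**What to change.** Settle the following in the analysis plan before any outcome data are examined:

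- **Antibiotic endpoint:** drop the per-protocol repeat, or report it only as a description of adherence.
- **Safety, adherence:** define it as receiving each component that the algorithm calls for on that patient's branch.
- **Safety, comparator:** state that all eligible usual-care patients are included.
- **Safety, overruled patients:** do not rely on simple deletion. At minimum, adjust the repeat for the covariates already listed for the intention-to-treat analysis (age, asthma, COPD, CRB-65, PSI).
- **Optional:** inverse-probability weighting on enrolment covariates, or an estimate based on assigned period, with assumptions stated. Weighting needs the covariates to capture why physicians overrule. An assignment-based estimate needs the switch to act only through adherence, which training and the ultrasound roll-out could breach.

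Cost: some analysis-plan text and one modest extra analysis. The article already provides for tracking non-adherence and for collecting clinical data at enrolment. The remaining weakness is that the adjusted or weighted result assumes no unmeasured reasons for overruling, and the report should say so.

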### Eligibility and exclusion criteria

All adult patients, aged 18 or older, presenting with an acute LRTI, are screened for inclusion by study nurses (SN) during working hours (weekdays 8am–5pm). Acute LRTI is defined, according to the European Society of Clinical Microbiology and Infectious Disease (ESCMID) guidelines [4], as an acute illness of less than 21 days, featuring at least one lower respiratory tract symptom, i.e., cough, sputum, dyspnea, or chest pain with no alternative explanation. Every consecutive patient meeting the inclusion and exclusion criteria detailed in Table 2 and providing a signed informed consent is included. SNs and/or physicians are responsible for collecting written patient’s informed consent for each participant.

**Table 2 Tab2:** Inclusion and exclusion criteria

Inclusion criteria	Exclusion criteria	
Patients aged 18 years or more	Previous receipt of a quinolone, macrolide, or ceftriaxone or more than one dose of any other antibiotic within 72 h prior to enrolment (excepted prophylactic antibiotics or antibiotics given for urinary tract infection)	
Acute LRTI (acute illness, less than 21 days, with at least one lower respiratory tract symptom, i.e., cough, sputum, dyspnea, chest pain, and no alternative explanation)	Acute care hospital stay in the previous 14 days	
At least one of the following clinical criteria:	Cystic fibrosis	
o Focal abnormal auscultation (decreased breath sounds, crackles, bronchial breath sounds)	Severe COPD (≥GOLD 3 or if not available, as a proxy: exacerbation treated with antibiotics during the last 6 months)	
o Fever (documented temperature ≥ 38°C in the last 24 h, including self-measured temperature ≥ 38°C)	Severe immunodeficiency (drug-induced neutropenia with <500 neutrophils/mm^3^, HIV infection with CD4<200 cells/mm^3^, solid organ or bone marrow transplant recipient, prednisone ≥ 20 mg/day for >28 days)	
o Tachypnoea (respiratory rate ≥ 24/min)	Initial admission of the patient in the intensive care unit	
o Tachycardia (heart rate ≥ 100/min	Microbiologically documented infection with SARS-CoV-2 (in the last 10 days)	
	Lack of decision-making capacity	

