### Blinding

Centers are randomly allocated to one cluster with pre-determined dates to switch from usual care (control group) to the intervention (intervention group). The assigned cluster was disclosed to the study centers in the month before initiating the study, as blinding is not feasible in this open-label trial. In this context, data analysts are not blinded either.

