#### Primary analysis

##### Primary safety and efficacy endpoints

Mixed effect generalized linear (logistic) models will be implemented in order to estimate the effect of intervention on safety (clinical failure) and efficacy (antibiotic prescription). The models will contain a random cluster level effect and a period specific fixed effect. Both intervention effects will be expressed in an odds ratio (OR) scale. A lower one-sided 95% confidence interval will be used in order to test effect significance for the safety outcome, reached when the upper bound of the interval is smaller than the non-inferiority margin (translated into the OR scale); a two-sided 95% confidence interval will be used to test effect significance for the efficacy outcome, reached when the interval does not contain the value of one.

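### The models that decide both co-primary endpoints leave out the patient-level factors the plan itself calls confounders, so a case-mix change at the switch, if one occurred, would bias both effects

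*Protocol article*

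**What the plan says.** - **Deciding models** (Protocol article, Primary safety and efficacy endpoints). Both co-primary endpoints are analysed by mixed logistic regression: "The models will contain a random cluster level effect and a period specific fixed effect". The non-inferiority and superiority rules are read from these models on the odds-ratio scale.
- **Patient-level factors** (Datasets to be analysed, analysis populations). The plan announces "Additional analysis adjusting for patient level confounding factors (age, asthma, chronic obstructive pulmonary disease, CRB-65, and PSI score"). It applies this step to the intention-to-treat set and to both co-primary endpoints. The same section plans analyses stratified by severity. It leaves a later plan for secondary, subgroup, stratified and sensitivity analyses, so the primary model is settled here.
- **Knowledge of allocation** (Blinding). Centers have "pre-determined dates to switch from usual care (control group) to the intervention (intervention group"), and "The assigned cluster was disclosed to the study centers in the month before initiating the study". The trial is open-label and the analysts are unblinded.
- **Recruitment** (Eligibility and exclusion criteria). Adults with acute LRTI "are screened for inclusion by study nurses (SN) during working hours"; nurses and/or physicians obtain consent. "Every consecutive patient meeting the inclusion and exclusion criteria detailed in Table 2 and providing a signed informed consent is included".

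**The concern.** The factors listed include severity scores, and sicker patients can be expected both to receive antibiotics more often and to fail more often. Patients enter one by one after everyone at the site knows which phase it is in. What participation involves also changes at the switch: after it, ultrasound has to be done by a study-certified physician and many patients have procalcitonin measured. Who is approached and who consents could therefore change at the same moment as the intervention.

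A within-center change that starts at the switch has the same pattern as the intervention indicator. Cluster terms remove stable differences between centers, and period terms remove calendar trends common to all centers; neither removes this. The Discussion says the design makes differing study populations less likely, but the reason given is differences between EDs, not a change inside one ED after it switches.

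At stake are both co-primary conclusions at once, in the same direction.

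**Working it through.** **1. The plan's own figures.** 15/0.9 = 16.7, rounded to 17; 17 × 9 × 10 = 1530, as stated. For power, the standard stepped-wedge variance (Hussey–Hughes) is

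Var = I·s²(s² + T·τ²) / [(I·U − W)s² + (U² + I·T·U − T·W − I·V)τ²],

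with I = 9, T = 10 and one switch per step, so U = 45, W = 285, V = 285. The two bracket coefficients are 120 and 660. The stated inputs are: "if the proportion of clinical failure is 20% in both groups, with a non-inferiority margin of 10"% , ICC 0.2, 15 patients per cell.

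- p(1−p) = 0.16 as total variance: τ² = 0.032, s² = 0.00853, SE = 0.0338, power = Φ(0.10/0.0338 − 1.645) = 0.91.
- 0.16 as within-cluster variance: τ² = 0.04, s² = 0.01067, SE = 0.0377, power = 0.84.

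The stated 80% is met. Sample size is not at issue.

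**2. Why the model cannot absorb a switch-timed shift.** The model is logit p = period(t) + θ·X(i,t) + u(i), with X = 1 after center i switches. A case-mix change at the switch adds approximately δ·X(i,t), so the model estimates θ + δ.

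**3. Size of δ.** Assumptions, none from the document: 30% of control patients are severe; severe versus non-severe odds ratio 2 or 3 for the outcome; the severe share falls by d after the switch; no true effect. Solve 0.7·p0 + 0.3·p1 = overall rate; the spurious change is d·(p1 − p0).

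| Endpoint (overall rate) | Prognostic OR | p0, p1 | Change at d = 10 points | Apparent OR |
|---|---|---|---|---|
| Failure (20%) | 2 | 0.165, 0.283 | −1.2 points | 0.93 |
| Failure (20%) | 3 | 0.143, 0.333 | −1.9 points | 0.88 |
| Antibiotics (65%) | 2 | 0.605, 0.754 | −1.5 points | 0.94 |
| Antibiotics (65%) | 3 | 0.583, 0.807 | −2.2 points | 0.91 |

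**4. Effect on the safety error.** The 10-point margin from 20% to 30% is an odds ratio of (0.3/0.7)/(0.2/0.8) = 1.714. The approximate one-sided error at the margin is Φ(bias/SE − 1.645), using both SEs above. Beside it are results from 600 simulated trials per scenario (9 × 10 × 15 patients, cluster SD 0.5 on the logit scale, cluster effects fitted as fixed in place of the random intercept).

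| Fall in severe share | Closed form, unadjusted | Simulated, unadjusted | Simulated, covariate in model |
|---|---|---|---|
| 0 | 5% | 5–7% | 4–6% |
| 5 points | 7–9% | 8–10% | 4–6% |
| 10 points | 9–14% | 9–15% | 4–6% |
| 15 points | 12–21% | 12–22% | 4–6% |

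Ranges span prognostic odds ratios 2 to 3. Monte Carlo error is about 0.9 points at 5% and 1.5 points at 15%. With a 10-point fall and prognostic odds ratio 3, the median estimate is 1.50 unadjusted and 1.73 adjusted, against a true 1.714.

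**5. Effect on efficacy.** True odds ratio 1, 10-point fall, prognostic odds ratio 3: the median estimate is 0.90 unadjusted and 1.00 adjusted. False superiority in the favourable direction is 7.3% against 2.8% (nominal 2.5%).

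**6. Scale.** With no shift at all, the adjusted odds ratio is slightly further from one than the unadjusted one (1.70 against 1.66 in simulation). An odds-ratio margin must therefore belong to the model that is used.

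**The case against.** The strongest reply is that the adjusted analysis already exists: it is prespecified for both endpoints in the intention-to-treat set, with severity-stratified analyses beside it. A gap between the two results would expose a shift in the measured factors. That is true, and it limits the point to which analysis decides. But the decision rules attach to the unadjusted models, and nothing says what follows if the two disagree.

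Second, enrolment is consecutive, screening is by study nurses rather than treating physicians, most clinical criteria are explicit thresholds that do not change between phases, and six interim monitoring visits per site focus mainly on safety and eligibility. This lowers the risk materially. It does not exclude it: enrolment is consecutive only among patients screened in working hours who consent, and the definition of LRTI includes a judgement that no other explanation applies.

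Third, unblinded staff record the covariates, and in the intervention phase the CRB-65 items also feed the algorithm's severity score. Recording could differ between phases, and adjustment could then add some bias. This stands as a caution. It is a reason to use values recorded at enrolment and to keep the unadjusted result in view.

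A reader might go further and infer that the primary results will be biased, that the bias will favour the algorithm, or that the plan ignores confounding. The document supports none of these. It shows no shift, a shift could run either way, and adjustment is planned.

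**Conclusion.** The point holds as a conditional one. The covariates the plan names as confounders are missing from the models that decide the trial, in a setting where a switch-timed change in recruitment is possible and the design terms cannot remove it. For a fall of 10 points in the severe share, the spurious effect would be 1.2 to 1.9 points on failure (against a 10-point margin) and 1.5 to 2.2 points on antibiotics (against a 15-point target). That is modest, but at the margin it is enough to double or nearly triple the nominal 5% safety error.

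The shift sizes, the 30% severe share, the prognostic odds ratios and the cluster SD are all assumptions. The direction reverses if sicker patients are recruited after the switch. The change is worth making because it is cheap protection, not because bias has been demonstrated.

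**What to change.** Before any outcome analysis:

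- Make the already planned covariate-adjusted model primary for both co-primary endpoints, with age, asthma, COPD and CRB-65 as recorded at enrolment added to the cluster and period terms.
- Leave PSI to a sensitivity analysis. The article does not list its items; as commonly scored it needs test results, and physicians order tests at their discretion, so its availability may differ between phases.
- Judge non-inferiority on a standardised risk difference from that model against the stated 10-point margin, or else define the odds-ratio margin for the adjusted model.
- Keep the current model as a prespecified sensitivity analysis, and report baseline characteristics by phase.

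Cost: demographics, comorbidities, vital signs and clinical signs are already collected at inclusion. The change needs a documented protocol amendment while the trial is running, with analysts who are not blinded, so its date relative to any look at outcomes should be recorded. A simple rule for missing covariates is needed. Selection on unmeasured factors would remain uncorrected.
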